# Focused Ultrasound and RadioTHERapy for non-invasive palliative pain treatment in patients with bone metastasis: a study protocol for the three armed randomized controlled FURTHER trial

**DOI:** 10.1186/s13063-022-06942-1

**Published:** 2022-12-29

**Keywords:** (MeSH): Cancer pain, Palliative care, Palliative therapy, Pain management, Neoplasm metastasis, Bone metastases, Radiotherapy, Radiation oncology, High-intensity focused ultrasound ablation, Magnetic resonance imaging interventional

## Abstract

**Background:**

Cancer-induced bone pain (CIBP), caused by bone metastases, is a common complication of cancer and strongly impairs quality of life (QoL). External beam radiotherapy (EBRT) is the current standard of care for treatment of CIBP. However, approximately 45% of patients have no adequate pain response after EBRT. Magnetic resonance image-guided high-intensity focused ultrasound (MR-HIFU) may improve pain palliation in this patient population. The main objective of this trial was to compare MR-HIFU, EBRT, and MR-HIFU + EBRT for the palliative treatment of bone metastases.

**Methods/design:**

The FURTHER trial is an international multicenter, three-armed randomized controlled trial. A total of 216 patients with painful bone metastases will be randomized in a 1:1:1 ratio to receive EBRT only, MR-HIFU only, or combined treatment with EBRT followed by MR-HIFU. During a follow-up period of 6 months, patients will be contacted at eight time points to retrieve information about their level of pain, QoL, and the occurrence of (serious) adverse events. The primary outcome of the trial is pain response at 14 days after start of treatment. Secondary outcomes include pain response at 14 days after trial enrolment, pain scores (daily until the 21st day and at 4, 6, 12 and 24 weeks), toxicity, adverse events, QoL, and survival. Cost-effectiveness and cost-utility analysis will be conducted.

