### Objectives

The aim of the FURTHER trial is to evaluate the effectiveness and cost-effectiveness of MR-HIFU (alone or in combination with EBRT) compared to EBRT alone for palliation of CIBP. The primary endpoint of this trial is patient-reported pain response 14 days after the start of treatment (Table 1). As MR-HIFU has been shown to be particularly fast acting (within 3 to 7 days [14–21]), compared to EBRT (4–6 weeks [6–8]). It is expected that patients suffering from cancer-induced bone pain could mainly benefit from MR-HIFU in the early weeks after treatment. Therefore, the primary endpoint was set at 14 days.

**Table 1 Tab1:** Primary and Secondary outcomes of the FURTHER-trial, a trial looking at the impact of treatment with MR-HIFU with or without radiotherapy on patients with painful bone metastases

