**Fig. 2 Fig2:**
[figure not shown]
Schematic overview of the follow-up timelines for the FURTHER trial illustrating the start and end of follow-up. In addition, the primary endpoint and secondary endpoint 14 days after inclusion are visualized. For all three arms, i.e., external beam radiotherapy (EBRT), magnetic resonance-guided high-intensity focused ultrasound (MR-HIFU), and EBRT + MR-HIFU, the follow-up is started after the first treatment session

Patients are free to leave the study at any time. Patients will be followed until death or end of study (6 months). To reduce the impact of patient death on loss to follow-up, the inclusion criteria “life expectancy > 3 m” was added. To further minimize missing data, patients will be actively contacted by phone on scheduled times to remind them of filling in the questionnaires. No specific dropout criteria are defined. The investigator can decide to withdraw a patient from the study for urgent medical reasons. Patients will be considered non-responders when they will be referred to alternative palliative treatments of the treated metastasis (such as (re)irradiation, radiopharmaceuticals, surgery, cryotherapy, radio-frequency ablation or nerve blocks, or MR-HIFU in the EBRT arm).

Since this study concerns a one-off treatment, patients will return to their general practitioner or referring oncologist. All participating centers have insurance that covers damage to research subjects through injury or death caused by the study. The insurance applies to damage that becomes apparent during the study or within 4 years after the end of the study.

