### Study procedures

#### Radiotherapy treatment

Control patients will undergo standard radiotherapy for painful bone metastases. The radiation schedule is at the discretion of the treating radiation oncologist. The radiation oncologist may decide to administer a single fraction EBRT of 8 Gy, a multi-fraction regime of 20 Gy in 5 fractions, 24 Gy in 6 fractions, or 30 Gy in 10 fractions. Fractions are standardly delivered once daily 5 days a week, making the total treatment length variable and span multiple days for multi-fraction treatment plans. A planning CT with or without contrast agent in treatment position will be taken for target delineation. Treatment plans may be delivered using intensity-modulated radiation therapy (IMRT), volumetric modulated arc radiotherapy (VMAT), or stereotactic body radiation therapy (SBRT) technique. Plans will be accepted if at least 90% of the planning target volume (PTV) will receive 95% of the prescribed dose (V90 > 95%). Typically, a 10-mm isotropic PTV margin will be used. A maximal 3D dose of 110% will be allowed. The maximum allowed dose in organs at risk will be determined according to the local institution’s protocol. Position verification is at the discretion of the treating radiation oncologist in consultation with the clinical physicist. It is encouraged to use online position verification by use of cone beam CT at every fraction.

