#### Combined treatment

Patients allocated to the combined intervention arm will undergo both interventions as described above. In our previous research, it was shown that the combined treatment of EBRT and MR-HIFU is feasible and safe [25]. Clinical outcomes were promising and need to be further assessed in this comparative trial.

In the combination treatment arm, both treatments will be planned as soon as possible following inclusion (preferably within one week), to ensure rapid pain palliation. The pre-treatment appointments will be planned in a way that is least burdensome for the patient. Therefore, flexible planning of preoperative screening and MR-HIFU treatment to minimize extra hospital visits is encouraged. To ensure an efficient workflow for the combined arm, a weekly available MR-HIFU slot is advised. The total treatment length is defined as the time between the first and last treatment session and depends on EBRT fractionation schedule and MR-HIFU availability.

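### Table 1 times the primary endpoint from completion of treatment, while the rest of the protocol times it from the start; a minor note on treatment order in the combined arm

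*Protocol article*

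**What the plan says.** **Anchor of the primary endpoint.** Objectives defines it as "patient-reported pain response 14 days after the start of treatment" and refers to Table 1. The abstract, Sample size calculation and Statistical analysis sections also count from the start. The Fig. 2 legend says that, for all three arms, "the follow-up is started after the first treatment session". Table 1, outcome 1.1, instead counts the 14 days from completion of treatment.

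**Length of treatment.** MR-HIFU is a single session. EBRT may be 1, 5, 6 or 10 fractions, and "Fractions are standardly delivered once daily 5 days a week" (Radiotherapy treatment).

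**Order in the combined arm.** The abstract describes "combined treatment with EBRT followed by MR-HIFU". The Combined treatment section gives no order. It says that "both treatments will be planned as soon as possible following inclusion (preferably within one week"), that "flexible planning of preoperative screening and MR-HIFU treatment to minimize extra hospital visits is encouraged", and that "a weekly available MR-HIFU slot is advised".

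**Why day 14.** Objectives explains the time point by speed: "MR-HIFU has been shown to be particularly fast acting (within 3 to 7 days"), against 4 to 6 weeks for EBRT. Pain is scored as the worst value over the previous 3 days.

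**The concern.** The two anchors coincide only when treatment is one session. For a multi-fraction course they differ by the length of the course, so the Table 1 rule gives longer EBRT courses more time to work than MR-HIFU alone. In a trial built on early relief, that moves the comparison towards the slower treatment. Objectives sends the reader to Table 1 and calls it the complete list of endpoints, so the conflicting definition is the one a reader is directed to.

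The start anchor, which is evidently the intended one, raises a smaller question. If EBRT is finished before MR-HIFU in the combined arm, a long course could leave MR-HIFU little time to act before day 14.

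**Working it through.** **Inputs.** Schedules of 1, 5, 6 and 10 fractions, one per weekday (Radiotherapy treatment); one MR-HIFU session (MR-HIFU treatment); response rates 0.69 and 0.40, 10% of MR-HIFU patients receiving EBRT instead, 10% dropout, 72 per arm, one-sided 5% (Sample size calculation).

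**1. Calendar.** Day 0 is the first fraction. I counted weekdays only, for each start day from Monday to Friday. The Table 1 read-out day for EBRT alone is the last-fraction day + 14. The last column is 14 − last-fraction day: the time left before a start-anchored day 14 if MR-HIFU is given on the day of the last fraction.

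| Fractions | Last fraction | Table 1 read-out, EBRT alone | Days left to day 14 |
|---|---|---|---|
| 1 | day 0 | day 14 | 14 |
| 5 | day 4 (Monday start) or 6 | day 18 or 20 | 10 or 8 |
| 6 | day 7 | day 21 | 7 |
| 10 | day 11 (Monday start) or 13 | day 25 or 27 | 3 or 1 |

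MR-HIFU alone is read at day 14 under either anchor. Under Table 1, 10-fraction EBRT therefore gains 25 − 14 = 11 or 27 − 14 = 13 days over MR-HIFU alone. Ten-fraction combined patients treated in the abstract's order are read at day 25 or 27 if MR-HIFU is on the last-fraction day, and later otherwise.

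**2. Time for MR-HIFU to act, start anchor, abstract's order, 10 fractions.** On the last-fraction day: 3 days (Monday start) or 1 day (any other start). On the next working day, MR-HIFU falls on day 14 itself, so 0 days. The best case only reaches the lower end of the stated 3-to-7-day onset, and the 3-day scoring window covers the days straight after the procedure. With MR-HIFU on the next working day, 6-fraction patients have 4 to 6 days and 5-fraction patients 7.

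**3. Effect on power.** Planned rate in the MR-HIFU arms: 0.9 × 0.69 + 0.1 × 0.40 = 0.661. Evaluable per arm: 72 × 0.9 = 64.8, taken as 65. Let a share f of the combined arm respond at 0.40, that is, with no MR-HIFU effect:

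- combined rate = 0.661 − f × 0.261, where 0.261 = 0.661 − 0.40
- pooled MR-HIFU rate = average of the combined rate and 0.661
- power from the pooled-variance z test for two proportions, one-sided 5%

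| f (assumed) | Combined − EBRT | Power, pooled 130 vs 65 | Power, combined vs EBRT 65 vs 65 |
|---|---|---|---|
| 0 | 0.261 | 96.9% | 91.7% |
| 0.10 | 0.235 | 95.4% | 85.7% |
| 0.25 | 0.196 | 92.0% | 72.5% |
| 0.50 | 0.131 | 83.0% | 43.8% |

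Pooled power reaches 90% at f = 0.318 with 130 vs 65, or 0.305 with 128 vs 64: about 31%.

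**The case against.** **On the anchor.** Four sections and the Fig. 2 legend agree on the start, so Table 1 is probably a slip and an analyst would probably follow the majority. That is likely. It does not make the table right: it defines the primary endpoint differently from the text that cites it.

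**On the order.** A reader might infer a design fault: that the combined arm cannot show its effect at day 14 and that the trial loses power for it. The document does not support that, for five reasons.

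- The order rests on the abstract's wording alone. The body sets none and encourages flexible MR-HIFU planning. With MR-HIFU before or between fractions, the short gap does not arise. The figure and the full protocol, which are not shown, may settle it.
- Order is not why one week is missed. Ten weekday fractions span at least 12 calendar days (day 0 to day 11) whichever treatment is first, and the target is only a preference.
- The share planned for 10 fractions is not given. It is one of four permitted schedules.
- The power table assumes no MR-HIFU effect at all in affected patients, although the Background says that response may occur within 3 days. If they kept half the effect, which is also an assumption, combined-versus-EBRT power would be 89.0%, 83.8% and 72.5% at 10%, 25% and 50% affected.
- The large losses concern a pairwise contrast for which the trial is not sized. Counting from the first session is also a fair way to compare strategies as delivered.

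Later data are planned too: daily scores to day 21, contacts from 4 weeks to 6 months that assess pain response, and a time-to-event analysis. Which later contrast is tabulated can be left to the analysis plan. These objections stand, and they reduce the sequencing matter to a note.

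**Conclusion.** Table 1, outcome 1.1, is wrong as written. Followed literally, it would read 10-fraction EBRT 11 or 13 days later from start than MR-HIFU alone. This rests only on the stated schedules and weekday delivery.

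The order in the combined arm is a minor point and conditional. If EBRT is completed first, 10-fraction patients have at most 3 days between MR-HIFU and day 14, and their result may largely reflect EBRT. How many patients this concerns cannot be told from the document. The sizing of the pooled primary comparison is robust: power stays at 90% or more until about 31% of the combined arm is affected, on the harshest assumption of no MR-HIFU effect in those patients.

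**What to change.** 1. Correct Table 1, outcome 1.1, to 14 days after start of treatment. This is a change of wording and costs nothing.
2. In the Combined treatment section, state the intended order, or state that day 14 compares strategies as delivered from the first session. This is also wording. A latest permitted day for MR-HIFU is not needed for this point; it would require an amendment and, with recruitment due to end on 10 March 2023, 71 days after publication on 29 December 2022, would reach few patients.
3. Optionally, show day-14 response by arm and planned fractionation, descriptively and without a test. Fractionation is already a randomization stratum, so the cost is one table on data already collected.

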**Discussion:**

The FURTHER trial aims to evaluate the effectiveness and cost-effectiveness of MR-HIFU—alone or in combination with EBRT—compared to EBRT to relieve CIBP. The trial will be performed in six hospitals in four European countries, all of which are partners in the FURTHER consortium.

**Trial registration:**

The FURTHER trial is registered under the Netherlands Trials Register number NL71303.041.19 and ClinicalTrials.gov registration number NCT04307914. Date of trial registration is 13–01-2020.

**Supplementary Information:**

The online version contains supplementary material available at 10.1186/s13063-022-06942-1.

## Background

Cancer-induced bone pain (CIBP) due to bone metastases often results in substantial deterioration of quality of life (QoL) in patients with advanced cancer [1, 2]. The mainstay of treatment of CIBP is oral analgesics (mostly opioids), in some cases stabilization or fixation surgery and in most cases external beam radiotherapy (EBRT) [3–5]. Although EBRT is a well-established treatment option, not all patients experience pain relief after this treatment. A recent systematic review has shown that approximately 45% of patients do not respond to EBRT and if patients do respond, it can take up to 6 weeks before adequate pain relief is reached. [6–8] Moreover, approximately 50% of initial responders experience recurrent pain, for which re-irradiation is only effective in 58% of patients [9, 10]. Fast and effective pain control is paramount to optimize QoL in palliative cancer care. Magnetic resonance image-guided high-intensity focused ultrasound (MR-HIFU), as an alternative or addition to EBRT, may improve pain palliation treatment in this patient population, by increasing the percentage of responders, and decreasing the time to response [11, 12].

MR-HIFU is a non-invasive treatment modality which can deliver acoustic energy to heat target tissue to ablative temperatures [11, 13]. One of many potential applications of MR-HIFU is in palliative pain treatment for CIBP, in which the pain palliation mechanism is hypothesized to be through ablation of periosteal nerves and tumor debulking. Previous studies have shown that pain response may occur within 3 days after MR-HIFU treatment, and response rates are promising with pain responses ranging from 67 to 88% of patients [14–21]. Moreover, combining MR-HIFU with EBRT may have a complementary or even synergistic effect on pain response [22–25]. In an earlier study, the feasibility of combined treatment was proven. [25]

Still, high-quality evidence and context are needed to determine the role of MR-HIFU in the first-line treatment options of patients with CIBP. The FURTHER consortium sets out to provide this evidence and to evaluate the effectiveness and cost-effectiveness of MR-HIFU (alone or in combination with EBRT) as a palliative treatment option for patients with CIBP caused by bone metastases. To date, no randomized controlled trials have been performed to compare the current standard of care (EBRT) to MR-HIFU or combined treatment. Therefore, we designed a three-armed randomized controlled trial with the objective to compare Focused Ultrasound and RadioTHERapy for Noninvasive Palliative Pain Treatment in Patients with Bone Metastases—The FURTHER trial.

## Methods

### Study design

The FURTHER trial is a multicenter three-armed randomized controlled superiority trial, performed in six hospitals in four European countries, all of which are partners in the FURTHER consortium. The trial will be coordinated from the UMC Utrecht, with a steering group consisting of representatives of all institutions and an external advisory board. The design and report of this protocol follow the Standard Protocol Items: Recommendations for Interventional Trials statement. [26]

After inclusion, patients are randomized in a 1:1:1 ratio to one of the three intervention arms and will receive either standard EBRT, MR-HIFU only, or combined EBRT and MR-HIFU (Fig. 1). Treatment will be delivered as soon as possible. A total of 216 patients will be randomized, 72 patients into each arm of the trial.

**Fig. 1 Fig1:**
[figure not shown]
Flowchart of the FURTHER-trial randomization design

### Intervention allocation

Randomization will be done centrally with a computer-generated sequence in Castor EDC [27]. Variable block randomization will be applied as allocation concealment mechanism. Randomization is stratified by institution and planned EBRT fractionation schedule. Patients and doctors will not be blinded to treatment and treatment allocation will not be concealed. Concealment of treatment allocation is not possible due to the evident differences between both MR-HIFU and EBRT interventions. Randomization will be performed during or after physical consultation on the Radiotherapy Department. Shortly after randomization, the patients will be informed about the randomization outcome and randomization arm-specific procedures, and treatment preparations will be started.

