### Sample size calculation

The study is powered to detect a difference in proportions of patients with pain response of the treated bone metastasis at 14 days after the start of treatment. For this purpose, the two MR-HIFU arms will be combined, and the sample size will be determined on a 2:1 comparison. We calculated we need 72 patients in each arm to achieve a power of 90%, using a one-sided alpha of 5% and assuming a 10% post-randomization dropout using R version 4.0.4 (R foundation for statistical computing; https://R-project.org/). We assume that the response rates during this trial will be similar to previous studies. Therefore, we base this calculation on previous research showing that the proportion of patients with successful pain palliation at 14 days following the start of treatment is 0.69 for MR-HIFU and 0.40 for EBRT [9, 14]. We conservatively assume that 10% of patients allocated to one of the MR-HIFU arms will not be able to undergo MR-HIFU and will therefore receive EBRT.

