### Statistical analysis

All statistical analyses will be performed using IBM SPSS statistics, version 24 (IBM Corp. Armonk, NY, USA) and R version 4.0.4 (R foundation for statistical computing; https://R-project.org/). Data characterized by normal distribution will be expressed as means with standard deviations. Parameters not normally distributed will be expressed as medians with the interquartile ranges. Data will be analyzed according to the intention to treat and per-protocol principle. In case of post-treatment dropout (i.e., patients not surviving longer than a week, or patients unable to provide pain scores and analgesic use), a worst-case analysis will be performed, where dropped-out patients will be classified as non-responders.

The domain of the primary outcome is pain response measured by the Brief Pain Inventory (BPI [28, 29]) at baseline and 14 days following the start of treatment. Pain response is defined as a reduction of pain score ≥ 2 points without an increase of analgesic intake, or a reduction of analgesic intake of ≥ 25% without an increase of pain score at the treated site. The method of aggregation is the proportion of patients with a complete or partial pain response between baseline and 14 days following the start of treatment. Differences in pain response between arms will be compared by *χ*^2^-test. We will also conduct a time-to-event analysis for pain response. Here, the method of aggregation is the median time to pain response. Survival analysis will be performed by the Kaplan–Meier estimate and is calculated as the number of subjects surviving divided by the number of patients at risk (proportion). Survival proportions will be compared at 6 months. Toxicity will be presented as the proportion of CTCAE grade 3–4 toxicity in the 6 months following the start of treatment and differences will be tested with the *χ*^2^-test. QoL will be expressed as the mean (or median) score on a scale of 0–100 (EORTC [31–35]) and compared between the three groups at 3 and 6 months after treatment starts. A mean change of 10% of the scale breadth from the baseline will be considered a clinically relevant change in QoL. We will evaluate the pattern of QoL as a continuous outcome over time using mixed models. Differences with a *P*-value of < 0.05 will be considered statistically significant. No additional subgroup analyses are planned.

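### The primary chi-square test ignores the stratification factors used in the randomisation; if they predict response, it is mildly conservative and gives up a little power

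*Protocol article*

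**What the plan says.** Intervention allocation: "Randomization is stratified by institution and planned EBRT fractionation schedule". Study design says the trial is "performed in six hospitals in four European countries". Radiotherapy treatment leaves the schedule to the treating radiation oncologist, who has four options: "a single fraction EBRT of 8 Gy, a multi-fraction regime of 20 Gy in 5 fractions, 24 Gy in 6 fractions, or 30 Gy in" (the last being a ten-fraction course). The protocol does not say how the four schedules are grouped for stratification.

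Statistical analysis: the primary outcome is summarised as the "proportion of patients with a complete or partial pain response between baseline and 14 days following the start of treatment", and "Differences in pain response between arms will be compared by" a chi-square test. No stratified test, covariate or adjusted estimate is named for this outcome, although mixed models are named for quality of life. Baseline enters through the endpoint itself: "Pain response is defined as a reduction of pain score ≥ 2 points without an increase of analgesic intake", or a 25% analgesic reduction without more pain.

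Sample size calculation: "the two MR-HIFU arms will be combined, and the sample size will be determined on a 2:1 comparison", with "72 patients in each arm to achieve a power of 90%, using a one-sided alpha of 5% and assuming a 10% post-randomization dropout". This too is an unadjusted comparison of two proportions.

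**The concern.** Blocking within strata forces the arms to be nearly balanced on institution and planned schedule. If those factors carry information about response, the arm difference varies less from one randomisation to the next than the simple two-proportion formula assumes. The chi-square standard error is then too large, the true significance level falls below nominal, and power is lost for no return.

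The factors could plausibly matter. A ten-fraction course given five days a week spans about 12 calendar days, so it has only just finished when pain is assessed 14 days after the start of treatment. The schedule is also the clinician's choice and may track differences between patients. Centres may differ in equipment, sedation and logistics. None of this is quantified in the protocol, so what is at stake is efficiency and the match between analysis and design, not validity.

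**Working it through.** **1. The plan's own figure.** The inputs come from Sample size calculation.
- Diluted MR-HIFU rate: 0.9 × 0.69 + 0.1 × 0.40 = 0.661. The EBRT rate is 0.40, so the difference is 0.261.
- 2:1 pooled comparison, pooled rate (0.40 + 2 × 0.661)/3 = 0.574, one-sided 5%, power 90%. EBRT n = [1.645·√(0.574 × 0.426 × 1.5) + 1.282·√(0.40 × 0.60 + 0.661 × 0.339/2)]² / 0.261² = 45.3, so 46 evaluable.
- 46/0.9 = 51.1, so 52 per arm. The stated 72 is not reproduced; the gap is on the generous side.
- At 72 per arm, 72 × 0.9 = 64.8, so 65 EBRT and 130 pooled MR-HIFU patients are evaluable. The standard error is 0.0751 with the pooled rate and 0.0736 with separate rates. One-sided power = Φ[(0.261 − 1.645 × 0.0751)/0.0736] = Φ(1.87) = 96.9%. Two-sided power is 93.9%.
- Pairwise, 65 versus 65, the standard errors are 0.0875 and 0.0845. One-sided power = Φ[(0.261 − 1.645 × 0.0875)/0.0845] = 91.7%. Two-sided power is 85.5%.

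**2. Assumptions for the stratum effect.** Twelve strata (six institutions × single or multiple fractions), permuted blocks within strata, and a normal stratum effect on the logit scale. Around a 40% response, strata one SD either side of the centre respond at about 29% and 52% for SD 0.5, 23% and 60% for SD 0.8, and 20% and 64% for SD 1.0.

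**3. Standard error and size of the plain test under the null (65 and 130; 8,000 replicates).** The approximate size is 1 − Φ(1.645 × model SE / true SD).
- SD 0.5: model SE 0.0739, true SD 0.0718, ratio 1.03. 1 − Φ(1.693) = 4.5%; simulated 4.4%.
- SD 0.8: model SE 0.0739, true SD 0.0690, ratio 1.07. 1 − Φ(1.762) = 3.9%; simulated 3.7%.

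Monte Carlo error is about √(0.05 × 0.95/8000) = 0.24 points. Separate runs place the size between 4.4% and 4.9% at SD 0.5, at about 3.8% at SD 0.8, and at about 3.5% at SD 1.0. The Cochran-Mantel-Haenszel (CMH) test stays near 5%.

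**4. Power, plain chi-square versus CMH.**

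| Stratum SD | Pooled 2:1, one-sided 5% | Pairwise, two-sided 5% |
|---|---|---|
| 0 | 96.8% vs 96.9% | 85.6% vs 86.2% |
| 0.3 | 96.7% vs 96.9% | not run |
| 0.5 | 96.9% vs 97.2% | 86.2% vs 87.7% |
| 0.8 | 97.4% vs 98.2% | 86.0% vs 89.0% |
| 1.0 | 91.4% vs 93.7% (see note) | 86.9% vs 90.4% |

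Note: this entry is from a separate run in which the protocol's log-odds ratio (about 1.07) was held within strata. That shrinks the marginal difference and lowers both powers. The comparison within the row is what matters. In the same set-up SD 0.5 gave 95.6% versus 96.0%.

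Both columns are shown because Statistical analysis speaks of arms without saying whether they are pooled, and gives a 0.05 threshold without sidedness.

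**5. Baseline pain.** With baseline pain prognostic (0.8 log-odds per SD) and no stratum effect, the plain SE is 0.0739 against a true SD of 0.0750, and one-sided size is 5.3%. The test is valid. Adjustment reduces the true SD to 0.0709, which is a precision gain only.

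**The case against.** **The loss is conditional.** With no stratum effect the two tests behave alike. No spread is given in the documents, and the ten-fraction argument applies only where EBRT is delivered. In the MR-HIFU-only arm the schedule is merely planned, so part of that mechanism is a varying treatment effect rather than a common shift. The listed MR-HIFU systems and sedation options are not assigned to centres either. All of this stands: the loss is possible, not established.

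**Power is not endangered.** A reader might infer an underpowered trial. For instance, a smaller effect (log-odds 0.75), a two-sided test and SD 1.0 give 54.1% versus 60.1%. That effect is not in the protocol, and the sample size is planned one-sided. On the protocol's inputs the plain test keeps more than 90% power for the pooled comparison even at SD 1.0.

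**Baseline pain.** A reader might also infer that leaving it out makes the standard error too wide. It is not a stratification factor, so the unadjusted standard error stays correct (step 5), and it already enters through the definition of response.

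**The analysis plan may settle it.** An article condenses, and adjustment is often specified in a statistical analysis plan, which is not shown here. That weakens any complaint about the missing adjusted estimate. It does not remove the point, because the protocol is not silent: it names a test, and that test does not reflect the randomisation.

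**Conclusion.** The mismatch is real and its consequence modest. If institution and planned schedule predict response, the stated test is conservative: roughly 4.9% to 3.5% true one-sided size for assumed SDs of 0.5 to 1.0. It forgoes about 0 to 2 power points in the pooled comparison and about 1 to 4 in a pairwise one. These figures rest on assumed values for the stratum spread, the number of strata (12) and the blocking; the response rates, dilution and dropout are the protocol's. Type I error is not inflated, and the 90% target for the pooled comparison is safe. The case for change is that analysing by the factors used to randomise costs essentially nothing when they do not matter and helps when they do. The gain counts most if arms are compared individually, where there is less spare power.

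**What to change.** Before outcome data are analysed, name as the primary test a Cochran-Mantel-Haenszel test stratified by institution and grouped planned fractionation (single versus multiple), or a logistic model with those factors as main effects. Report the risk difference with its 95% confidence interval, and keep the plain chi-square as a sensitivity analysis. Baseline worst pain, already collected, may be added to the model for precision only.

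The cost is a change of wording, with no new data and no change to conduct. The one downside is sparse strata. Crossing six institutions with all four schedules gives 24 cells, or 216/24 = 9 patients each on average; two fractionation groups give 12 cells and 18 each. State in advance how small centres or schedules will be pooled, or use main effects.
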